#### 2.8.2. Secondary Outcome

“*Discomfort Caused by Acupuncture Therapy*” *Five Questions*. On the basis of the results of a previous study [14] on sham acupuncture treatments in healthy individuals, five questions were used to evaluate the discomfort caused by acupuncture therapy. This questionnaire consists of questions on (1) the general perception of acupuncture, (2) discomfort at the moment of puncture, (3) the location of the feeling of puncture, (4) the intensity of discomfort, and (5) the duration of the puncture sensation. Four questions (i.e., general perception of acupuncture, discomfort at the moment of puncture, location of the feeling of puncture, and location of the feeling of puncture) will be answered as either “yes” or “no.” For intensity of discomfort, the 11-point numerical scale, ranging from 0 (no discomfort) to 10 (worst discomfort), will be used. The question on duration of the puncture sensation will be answered in minutes or seconds, and the record will be in seconds.

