**Methods:**

The proposed study is a single-center, prospective, randomized sequence, participant- and assessor-blinded trial with four parallel arms. A total of 90 participants will be randomly assigned to Group 1, Group 2, Group 3, or Group 4 in a 1 : 1 : 1 : 1 ratio. All groups will be treated with Quchi (LI11) for 20 minutes. Group 1 will be treated with verum acupuncture; Group 2, with Park Sham Device; Group 3, with Streitberger's needle; and Group 4, with insertion- and removal-type devices. Participants will undergo one treatment session. The primary outcome is Bang's blinding index. Secondary outcomes are the “Discomfort caused by acupuncture therapy” questionnaire and the Massachusetts General Hospital Acupuncture Sensation Scale index. Immediately after the procedure, all participants will also be monitored for adverse events.

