### 2.7. Interventions

#### 2.7.1. Study Flow and Treatment Procedure

Acupuncture treatment will be performed once during the trial. The acupuncture treatment will be carried out by a practitioner with more than 2 years of clinical experience. Before the treatment procedure, the patient's basic characteristics (e.g., age, sex, body mass index (BMI), vital signs, past medical history, drug consumption, education, occupation, alcohol consumption, smoking habit, and stroke type (cerebral infarction or cerebral hemorrhage), MMSE-K, National Institute of Health Stroke Scale (NIHSS) score, and Modified Rankin Scale will be investigated.

The entire procedure will be performed over 20 minutes. After all of the preparations for treatment are complete, the participants will be asked to lie on the bed for 2–5 min to stabilize. In the verum acupuncture group, real manual acupuncture will be performed. In the three sham acupuncture groups, Park Sham Device, Streitberger's needle, or insertion- and removal-type acupuncture will be applied. Details of the acupuncture treatment are described in the Standards for Reporting Interventions in Clinical Trials of Acupuncture (STRICTA) checklist in Table 1. During the entire trail period, all the procedures of acupuncture will be carried out by one practitioner who is independent. During the procedure, a prepared visual barrier will prevent participants from viewing their arm and confirming the type of acupuncture. Immediately after the end of the procedure, a questionnaire for determining Bang's blinding index and the “Discomfort caused by acupuncture therapy” questionnaire will be administered, and the Massachusetts General Hospital Acupuncture Sensation Scale (MASS) index, by deqi sensation, will be determined (Figure 1).

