	Precise description of the control or comparator. If sham acupuncture or any other type of acupuncture-like control is used, provide details as for items 1 to 3 above	The allocation for control groups (Groups 2∼4) will be decided by randomization (Group 2) 1) Park Sham Device: 0.25 × 40 mm sterilized stainless steel needle (Park Sham Device, AcuPrime, Exeter, UK) will be used Group 3: Real Streitberger's needle; 0.25 × 40 mm sterilized stainless steel needle (Asia-med GmbH & Co. KG, [name], Germany) Group 4: verum acupuncture needle; 0.25 × 40 mm sterilized stainless steel needle (Dong Bang Acupuncture, Gyeonggi-do, Korea). After puncture, remove immediately without retention The appearance, acupuncture point, stimulation method, and duration will be the same as the real acupuncture group (Group 1) Besides using sham needle tools, all procedures are the same, including acupuncture therapy, stimulation method, and frequency of stimulation

STRICTA: Standards for Reporting Interventions in Clinical Trials of Acupuncture.

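### Duration of the puncture sensation is asked once, right after the 20-minute session, and analysed as complete, with no provision described for a sensation still present (minor, secondary item)

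*Protocol article*

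**What the plan says.** Protocol article, section 2.7.1: "Acupuncture treatment will be performed once during the trial", and "The entire procedure will be performed over 20 minutes". The same section fixes the time of assessment: "Immediately after the end of the procedure, a questionnaire for determining Bang's blinding index and the “Discomfort caused by acupuncture therapy” questionnaire will be administered". The Abstract gives the same treatment time for every arm: "All groups will be treated with Quchi (LI11) for 20 minutes".

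Section 2.8.2 lists five discomfort items and their response formats: yes or no, a 0–10 scale and, for the last item, a time: "The question on duration of the puncture sensation will be answered in minutes or seconds, and the record will be in seconds". It describes no response for a sensation that has not ended.

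Section 2.11 states that the five questions and the MASS index are compared between groups by ANOVA, and that no sensitivity analysis will be done. No later contact for this item is described anywhere. Section 2.15 also places the adverse-event enquiry immediately after treatment.

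**The concern.** A participant who still feels the puncture when questioned has no completed duration to report. The answer is either the time elapsed since puncture, which is a right-censored value, or a guess. Stored as plain seconds, it looks the same as the answer of someone whose sensation really ended at that time, and ANOVA treats the two alike.

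This matters because section 2.1 makes the response to each sham, compared with real acupuncture, part of the objective, and the hypothesis in section 2.11 is about which sham feels most like verum. Duration is the only time-based measure of that response. If ongoing sensations are concentrated in the arm with the longest sensation, the cut shortens that arm most, and the recorded means lie closer together than the true ones. In a study looking for similarity, that error is easily read as a result. Whether a sensation was ongoing is known only when the question is asked and cannot be reconstructed later.

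**Working it through.** **Inputs from the article.** One session; procedure of 20 minutes; questionnaire immediately afterwards (section 2.7.1). Rest before needling: "the participants will be asked to lie on the bed for 2–5 min to stabilize" (section 2.7.1). At least 22 per group (section 2.10). Comparison by ANOVA at the 5% level (section 2.11).

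**Assumption.** The article gives no mean, spread or share still ongoing for this item, so a range of true means is used.

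**Step 1: the longest duration that can be observed.** 20 × 60 = 1200 s. If the rest lies inside the 20 minutes, it is (20 − 5) × 60 = 900 s to (20 − 2) × 60 = 1080 s. The text does not settle which.

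**Step 2: effect on a difference in means.** With true duration T and cut-off c, the recorded value is min(T, c). The recorded difference equals the true difference minus the gap between the arms in mean time lost beyond c. It therefore shrinks when the arm with the longer mean also loses more time beyond c.

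**Step 3: size under exponential durations with mean m.** Recorded mean = m(1 − exp(−c/m)); share still ongoing = exp(−c/m). With c = 1200 s:

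| True mean (s) | Share ongoing | Recorded mean (s) |
|---|---|---|
| 1200 | 0.368 | 759 |
| 600 | 0.135 | 519 |
| 300 | 0.018 | 295 |
| 120 | under 0.001 | 120 |

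| Arms compared (s) | True difference | Recorded difference | Lost |
|---|---|---|---|
| 1200 vs 600 | 600 | 240 | 360/600 = 60% |
| 600 vs 300 | 300 | 224 | 76/300 = 25% |
| 300 vs 120 | 180 | 175 | 5/180 = 3% |
| 60 vs 20 | 40 | 40 | none |

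With c = 900 s the first two recorded differences are 633 − 466 = 167 s and 466 − 285 = 181 s.

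**Step 4: another shape.** With lognormal durations (log-SD 1) and c = 1200 s, simulation keeps 0.43, 0.69, 0.89 and 1.00 of the true difference in the same four comparisons.

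**Step 5: power.** One-way ANOVA was simulated with 22 per arm, 2000 runs, one arm at 1200 s and three at 600 s. Power went from 0.66 uncut to 0.48 cut under the exponential, but from 0.47 to 0.59 under the lognormal, where the cut also removes outliers. The direction is not fixed.

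**Step 6: what a censored analysis changes.** The area under a Kaplan-Meier curve up to 20 minutes is the mean of min(T, 1200), so it returns the same 759 and 519 s. In a separate simulation of the same setting, log-rank power was close to that of ANOVA on the cut values: 0.50 against 0.46 (exponential) and 0.54 against 0.59 (lognormal).

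**The case against.** The strongest objection is that the problem may never arise. The item concerns a puncture sensation, Table 1 gives one insertion with simple puncture as the response sought, and an answer in minutes or seconds suggests that short durations are expected. At means of 300 s or less the exponential loss is about 3%, and the lognormal case at 300 against 120 s loses 11%. This stands: the 60% figure needs a mean of 20 minutes in one arm, which nothing in the article supports.

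Second, the case report form is not shown. A reader might infer that it has no box for a sensation still present, but the article shows only that none is described. This also stands. A box alone would not settle the matter, however, because the ANOVA in section 2.11 would still take the seconds as complete.

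Third, a reader might infer that verum lasts longest and that the shams will therefore look too similar to it. The article gives no durations by arm, and its Introduction warns that sensation in paralysed limbs may differ from that in healthy people. The direction by arm is plausible but not documented. Nor need the cut be sharp, since some participants may guess.

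Fourth, time felt within the session is a legitimate measure, and Kaplan-Meier methods cannot recover what happens after 20 minutes. Both are correct. But the article calls the item duration of the sensation, not duration within the session, and does not describe separating ended from ongoing answers. That much of the point remains.

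**Conclusion.** The point holds in a limited form. The single assessment, its timing, the record in seconds and the ANOVA are all stated. It follows that any sensation still present is cut off at about 1200 s (900 to 1080 s if the rest is included) or guessed, and is then analysed as complete. Where the longer-lasting arm has more of these, the recorded mean difference understates the true one.

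The size is unknown. Under the assumed distributions it runs from nothing, when sensations last seconds, to 60% of the difference at 1200 against 600 s. The documents do not support saying that the trial will find a sham falsely similar to verum, or that the test will lose power.

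A common cut-off also requires every arm to be questioned at the same time after puncture. For Group 4, Table 1 says "After puncture, remove immediately without retention" and also states the same duration as Group 1, while the Abstract gives all groups 20 minutes. These passages, and the place of the rest period, must be reconciled before the cut-off is known for each arm.

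This is minor: one item of one secondary questionnaire. Bang's blinding index is not touched.

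**What to change.** - Add an entry for a sensation still present at the time of asking to the duration question in section 2.8.2, or state that the form already has one.
- Report the share still feeling the puncture in each arm. This alone shows whether the cut-off mattered.
- In section 2.11, treat those answers as censored at the time of asking, with Kaplan-Meier curves and a log-rank test or hazard ratio, in place of ANOVA on seconds taken as complete.
- Describe any mean that is reported as duration within the 20-minute session.

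The cost is one tick box and slightly more analysis, with no extra visit. It does not recover durations beyond 20 minutes and should not be expected to raise power. Its value is that a truncated time is not read as a true duration or as evidence of similarity to verum.

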### 2.9. MASS Index

The MASS index by deqi sensation will also be conducted. It is an index of the 12 total sensations caused by acupuncture (i.e., treatment soreness, aching, deep pressure, heaviness, fullness/distention, tingling, numbness, sharp pain, dull pain, warmth, cold, and throbbing). The MASS index is calculated based on the findings of Kong et al. [19]. Because there is no Korean version, the MASS index, a Japanese version of MASS [20], will be translated and used, as Japan and Korea are countries with very similar cultures and lifestyle.

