In most clinical studies in stroke patients, acupuncture treatment is usually applied to the paralyzed acupoint. However, the paralyzed limbs of stroke patients have complex patterns of muscle tone, muscle strength, and sensory abnormality [17], and there could be differences in the degree of sensitivity during stitching and the discomfort felt during acupuncture treatment compared to those in healthy individuals. Therefore, it is difficult to apply the validation results of sham acupuncture treatments, evaluated in healthy individuals, to stroke patients. However, there has been no study that has evaluated which type of sham acupuncture is suitable for a study population of stroke patients. In addition, even in acupuncture-related clinical trials involving similar stroke types, there are limitations to performing a meta-analysis because of the different types of sham acupuncture treatments used in each study.

In this study, we will evaluate the success rate of blindness and the posttreatment response to sham acupuncture treatments (three types) compared with verum acupuncture treatment in hemiplegic stroke patients. To assess the success blinding rate of various sham acupuncture treatments, a randomized, double-blinded (participants and evaluator), 4 group paralleled clinical trial will be conducted. Through this study, we aim to explore the most appropriate sham acupuncture tool for clinical research on stroke.

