### 2.11. Statistical Analysis

Hypothesis to be tested in this study is that the certain sham device will reveal the most similar sensation to verum acupuncture in the affected limb of stroke patients. Primary outcome of this study is Bang's blinding index in each group. The value of Bang's blinding index of each sham acupuncture device will be calculated by comparison with the verum acupuncture group. This statistical process will be based on Bang's previous study, published in 2004 [18]. In secondary outcome analysis, the values of “Discomfort caused by acupuncture therapy” five questions and MASS index will be compared by ANOVA. In baseline characteristics, categorial variables will be compared by a chi-square test and continuous variables will be compared by ANOVA. A comparative analysis of the frequency of patients with sensory disturbances by each group will evaluate whether stratification assignments have been made properly. In subgroup analysis, we will compare the values of primary and secondary outcomes in patients with sensory disturbances. Patients with sensory disturbances are defined as patients who complaint sensory disturbances such as numbness, hypesthesia, or paraesthesia in affected limbs. In this study, sensitivity analysis will not be performed. A 5% significance level will be used. Study data will be analyzed using the Statistical Package for the Social Sciences (SPSS) software, version 16.0, for Windows and Microsoft Excel 2010 for windows by a blinded statistician.

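### MASS is rated only after needling of the affected limb, so numbness and tingling already present from the stroke can be scored as needle sensation and make the devices look more alike

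*Protocol article*

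**What the plan says.** Section 2.9 describes the MASS in these words: "It is an index of the 12 total sensations caused by acupuncture". After soreness, its items are "aching, deep pressure, heaviness, fullness/distention, tingling, numbness, sharp pain, dull pain, warmth, cold, and throbbing".

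The timing is set in one sentence of section 2.7.1. It opens "Immediately after the end of the procedure, a questionnaire for determining Bang's blinding index" and ends "and the Massachusetts General Hospital Acupuncture Sensation Scale (MASS) index, by deqi sensation, will be determined". What is collected beforehand is introduced by "Before the treatment procedure, the patient's basic characteristics". The examples that follow include MMSE-K, NIHSS and the Modified Rankin Scale, but no rating of sensations in the limb. Table 1 puts the single needle at LI11 on the affected side.

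Section 2.11 defines sensory disturbance as applying to "patients who complaint sensory disturbances such as numbness, hypesthesia, or paraesthesia in affected limbs". The Introduction justifies the trial partly on the ground that "the paralyzed limbs of stroke patients have complex patterns of muscle tone, muscle strength, and sensory abnormality".

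Section 2.5 stratifies randomisation by presence or absence of sensory disturbance in the affected limb. Section 2.11 compares the MASS by ANOVA and plans a subgroup analysis of patients with sensory disturbance.

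**The concern.** Numbness appears both as a MASS item and in the protocol's definition of a symptom present before treatment. Tingling is a MASS item that corresponds to paraesthesia in that definition. A patient whose arm was already numb may report numbness after any device. With one rating after the procedure, the score cannot be divided into what the needle caused and what was there before.

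This matters because section 2.11 frames the hypothesis as similarity of sensation to verum in the affected limb. Background symptoms common to all arms add variance between patients. If a patient reports whichever source is stronger, they also hide a weaker needle sensation. Both effects make the arms harder to tell apart, and in a search for the most verum-like sham that could be read in a device's favour. A pre-needling rating that was never taken cannot be recovered in the analysis.

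**Working it through.** **The plan's own figure.** Section 2.10 gives at least 22 per group and 90 in total: 4 × 22 = 88, plus 2 for withdrawal = 90. The number comes from a study in healthy people, without a power calculation, so there is no planned power to reproduce. I use 22 per arm below, with the 5% level of section 2.11 taken as two-sided.

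**Overlap.** For numbness it is explicit (sections 2.9 and 2.11). For tingling it is close, through paraesthesia. For heaviness, aching, dull pain and cold it is clinical inference, and nothing below depends on it.

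**Added variance.** Assumed, because the documents give no values: needle-induced index SD 1.5 (variance 2.25); half the patients with background symptoms; background adds to the score with mean m and SD s.

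- Without adjustment, the added variance is 0.5·s² + 0.25·m².
- With a stratum term, if the strata match the patients with background, the 0.25·m² part is removed and 0.5·s² remains.
- Within the sensory-disturbance subgroup, if all have background, the added variance is s².
- Information lost = 1 − 2.25 / total variance.

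| | m = 1, s = 0.5 | m = 2, s = 1 |
|---|---|---|
| Unadjusted | 2.25 + 0.125 + 0.25 = 2.625; 14% lost | 2.25 + 0.5 + 1 = 3.75; 40% lost |
| Stratum term | 2.25 + 0.125 = 2.375; 5% lost | 2.25 + 0.5 = 2.75; 18% lost |
| Subgroup only | 2.25 + 0.25 = 2.5; 10% lost | 2.25 + 1 = 3.25; 31% lost |

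**Power.** Take a true verum-sham difference of 0.85 needle-sensation SDs, which 22 per arm detects with about 80% power when there is no background. With r the ratio of background variance to needle-sensation variance, power = Φ(0.85·√11/√(1 + r) − 1.96).

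- r = 0: Φ(0.859) = 0.81.
- First column of the table: r = 0.375/2.25 = 0.17 unadjusted, power 0.74; r = 0.125/2.25 = 0.06 with the stratum term, power 0.78.
- Second column: r = 1.5/2.25 = 0.67 unadjusted, power 0.59; r = 0.5/2.25 = 0.22 with the stratum term, power 0.72.

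**Gain from a pre-needling rating.** If the rating captures the background with reliability 0.8 (assumed), r is replaced by r·(1 − 0.8). At r = 0.5 power goes from 0.63 to 0.77, and at r = 1 from 0.51 to 0.73.

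**Masking.** This was simulated for one 0–10 item: needle sensation mean 3 (verum) against 1.3 (sham), SD 2; background mean 4, SD 2; the patient reports the stronger of the two; no stratum term. Power was 0.77, 0.50, 0.33 and 0.20 with 0, 25, 50 and 75% of patients affected. This shows the mechanism on a single item. It is not an estimate for a 12-item index.

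**The case against.** The protocol anticipates the confounder. It stratifies on it, checks the balance and plans a subgroup. This stands to the extent that no device is favoured, and a reader who inferred bias toward one sham would be wrong. A stratum term would also remove much of the added variance. None is stated, but covariates are commonly left to an analysis plan, which is not shown, so its absence is no fault. A yes/no stratum still does not capture how severe the symptoms are.

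The pre-treatment list is given as examples in a condensed article, and the rating instructions are not shown. That is fair. The MASS itself, however, is placed only after needling.

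A reader might infer that the subgroup suffers most. Under additive background it does not: the share lost is 10% to 31%, below the unadjusted 14% to 40% for the whole trial. Only masking would support that reading. Nor do the documents support the idea that masking reduces differences to zero. That needs background at least as strong as the verum sensation, item by item, and the MASS covers 12 sensations.

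Some masking is arguably what the trial studies: if a numb limb cannot tell sham from verum, that bears on suitability. This is right for perception. It does not justify counting old numbness as a sensation produced by the device.

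Finally, showing patients needle sensations in advance could shape the guess that forms the primary outcome. This is a good reason not to give the full 12-item list before treatment. Asking patients for new or stronger sensations also relies on a separation that they may make poorly, so wording alone is not enough.

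**Conclusion.** The point holds for the MASS. Its timing, the needled limb and the overlap in numbness and tingling all follow from the protocol, and the separation of old from new sensation cannot be restored afterwards. The effect is lost precision and possible attenuation, shared by all arms.

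Its size is unknown. Under the assumed SDs and half the patients affected, 14% to 40% of the information is lost unadjusted and about 5% to 18% with a stratum term. The lower range assumes that the strata coincide with the patients who have background symptoms.

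Two stronger readings are not supported. The primary outcome is not compromised by this, because Bang's index is not scored from the MASS. Nor does section 2.11 say that a non-significant ANOVA will be taken as proof of similarity. For a secondary outcome, the point is minor to moderate: worth changing because the change is cheap and must be made before data collection.

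**What to change.** 1. When sensory disturbance is established for stratification, before randomisation, have the overlapping symptoms in the affected arm (at least numbness and tingling) rated once on the MASS item scale. Present them as existing stroke symptoms, not as sensations that a needle might cause.
2. Compare the MASS between groups by ANCOVA with that rating and the sensory-disturbance stratum as covariates. In the sensory-disturbance subgroup, use the rating alone.
3. After the procedure, instruct patients to rate sensations that are new or stronger than before needling.
4. State that the blinding question is asked before the MASS, which is the order in which section 2.7.1 lists them.

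The cost is a rating of a few items in a session that already includes MMSE-K and NIHSS, two covariates, and one added instruction in an instrument that is being translated anyway. A small priming risk remains, limited by the framing and the question order. The covariates recover precision. They do not restore a needle sensation that was fully masked, for which the instruction is only a partial help.
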